#### Rare (< 0.1%) side effects:

*Gastrointestinal:* Adult tooth staining (at least 1 case)

#### Frequency not reported:

*Hematologic:* Hemolytic anemia, thrombocytopenia, neutropenia, eosinophilia

*Metabolic and Nutritional:* Hypoglycemia, anorexia

*Infections and Infestations:* Possible overgrowth of nonsusceptible organisms (superinfection)

*Renal and Urinary:* Dose-related rise in BUN

*Reproductive Disorders:* Vaginal itch, vaginal candidiasis

*Hepatic and Biliary:* Acute hepatocellular injury, cholestatic reactions, hepatotoxicity

*Body as a whole – general:* Microscopic brown-black discoloration of the thyroid gland

*Dermatologic:* Nail discoloration, phototoxicity, photoallergic reaction, photo-onycholysis, photosensitivity, maculopapular and erythematous rashes, erythema multiforme, Stevens-Johnson syndrome, toxic epidermal necrolysis, exfoliative dermatitis, hyperpigmentation

*Gastrointestinal:* Clostridium difficile associated diarrhea, esophageal irritation, ulceration, epigastric burning, black hairy tongue, Esophagitis and esophageal ulcerations (most took medication immediately before going to bed)

*Nervous system:* Sinus headache, dizziness, drowsiness, amnesia, paresthesias of body areas exposed to sunlight, phrenic nerve paralysis after sclerotherapy, benign intracranial hypertension resulting in significant loss of vision

*Ocular:* Diplopia, papilledema, loss of vision (associated with doxycycline-induced benign intracranial hypertension)

*Hypersensitivity:* Hypersensitivity reactions (including urticaria, angioneurotic edema, anaphylaxis, anaphylactoid purpura, serum sickness, pericarditis, exacerbation of systemic lupus erythematosus, drug rash with eosinophilia and systemic symptoms [DRESS])

*Immunologic:* Autoimmune syndromes

Postmarketing reports:

*Nervous system:* Pseudotumor cerebri (benign intracranial hypertension), headache

### **9.5.2 Precautions to mitigate drug specific risks (Doxycycline)**

Photosensitivity

Photosensitivity manifested by an exaggerated sunburn reaction has been observed in some individuals taking tetracyclines. Patients apt to be exposed to direct sunlight or ultraviolet light will be advised that this reaction can occur with tetracycline drugs. Treatment will be immediately stopped at the first evidence of skin erythema.

Growth and Development

All tetracyclines form a stable calcium complex in any bone-forming tissue. A decrease in fibula growth rate has been observed in prematures given oral tetracycline in doses of 25 mg/kg every six hours. This reaction was shown to be reversible when the drug was discontinued. Results of animal studies indicate that tetracyclines cross the placenta, are found in fetal tissues, and can have toxic effects on the developing fetus (often related to retardation of skeletal development). Evidence of embryotoxicity also has been noted in animals treated early in pregnancy. If any tetracycline is used during pregnancy or if the patient becomes pregnant while taking these drugs, the patient should be apprised of the potential hazard to the fetus. Therefore women taking part in the clinical trial will be informed in detail about the risk associated with a pregnancy during drug intake. Pregnancy tests will be carried out every week and if a positive pregnancy test occurs against all precautions, treatment will be stopped immediately.

Clostridium difficile –associated diarrhea

Clostridium difficile-associated diarrhea (CDAD) has been reported with the use of nearly all systemic antibacterial agents, including Moxifloxacin, with severity ranging from mild diarrhea to fatal colitis. Therefore participants in this trial with diarrhea will be monitored especially for CDAD and in case of suspected or confirmed CDAD treatment will be immediately stopped and the patient will be treated for CDAD as appropriate (fluid and electrolyte management, protein supplementation, antibacterial treatment of C. difficile, surgical evaluation if clinically indicated) until recovery. Since CDAD has been reported to occur over two months after the administration of antibacterial agents, patients will be

strongly encouraged to report any severe diarrhea to the research team also after completion of the treatment.

### Superinfection

As with other antibiotic preparations, use of this drug may result in overgrowth of non-susceptible organisms, including fungi. If superinfection occurs, treatment will be immediately stopped and appropriate therapy instituted until recovery.

### Benign Intracranial Hypertension (pseudotumor cerebri)

Bulging fontanelles in infants and benign intracranial hypertension in adults have been reported in individuals receiving tetracyclines. These conditions disappeared when the drug was discontinued. Therefore treatment of patients with a suspected benign intracranial hypertension (e.g. headache associated with gradual visual field defects, nausea, vomiting, drowsiness) will be stopped immediately and appropriate therapy will be given until full recovery.

## **9.5.3 General precautions and warnings**

### Pregnancy and breastfeeding:

To avoid any complications, pregnant or breastfeeding women will be excluded from the clinical trial. Pregnancy tests will be carried out during the screening and right before the first treatment. Additionally, pregnancy tests will be repeated after three and six weeks of treatment. In case of pregnancy in any group, treatment will be stopped immediately. All women will be informed in detail about the risks of getting pregnant during the informed consent procedure and their obligation and responsibility to use effective contraceptive methods excluding daily hormonal contraception as the trial drugs can reduce their efficacy.

## **9.6 Blistering and Labeling of the IMP**

Blistering and labeling of the trial drugs will be done by Piramal Healthcare, Morpeth, United Kingdom. All IMPs will be blistered and labeled for the conduct of clinical trials only.

## **9.7 Transport of IMP**

The trial drugs will be delivered to the trial sites by plane and car at appropriate conditions (temperature not above 25°C).

## **9.8 Handling of IMP at the Site and Drug Accountability**

All study drug will be kept in a secure cabinet or a room with access restricted to the responsible study personnel. Medication must be stored at appropriate conditions (temperature not above 25°C). The storage and handling of all study medication will be supervised by the study pharmacist.

The study pharmacist will be responsible for maintaining accurate records of receipt of all study medication as well as of all medication dispensed to and used by each patient.

At the completion of the study, all unused medication will be destroyed once drug accountability is complete.

## **9.9 Strategies to improve adherence and compliance**

Both doxycycline and placebo will be administered under supervision throughout the treatment period (directly observed treatment). Ideally, patients will be required to come every day to the meeting point in their village to take their drugs under supervision. In case a patient is not present for the DOT, the drugs will be handed out to a village health worker or a family member and the intake by the patient

will be checked at the following day when the patient will have to give back the empty package and the village health worker or family member will be asked to witness the intake. In some cases, patients have to travel for a few days. When they proved their compliance before, the drugs for the travel days will be handed out to the patient and compliance will be reviewed by getting back the empty packages when the patient comes back from travel. In this case the patient will be asked to immediately report any adverse reactions or problems with the trial drugs by mobile phone to the trial clinician or to contact a village health worker or the nearest health facility who will then call the research team. All patients will be counseled at the time of the initial dose and during the treatment period. Key messages will include:

- The importance of following study guidelines for adherence
- Instructions about taking study pills whole, and what to do in the event of a missed dose.
- Reinforcement that study pills may be doxycycline or placebo
- Emphasize that all participants are expected to benefit from the hygiene intervention.
- Importance of contacting the research team if experiencing problems possibly related to study product
- Patients will be questioned about problems with the drugs and motivated to complete treatment as planned
- In addition, patients will be visited once every two months in the follow-up period to record the occurrence of ADLA attacks and reinforce the hygiene routine.

## 9.10 Unblinding

The patient, the investigators and all other site staff will be kept blinded throughout the study. All assessments of the patient will be made without knowledge of the treatment and every effort must be made to maintain the blinding. Unblinding will only occur in the case of medical emergencies or pregnancy and only if knowledge about the administered study drug is expected to improve the patient's treatment.

## 9.11 Prior and Concomitant Therapy/Medication

### 9.11.1 Previous therapy / medication of trial specific illness

All previous treatments for managing LE (e.g. Mass drug administration, previous rounds of IVM and/or ALB, last intake of IVM, last intake of ALB) and applied medications will be documented in the CRF according to the memory of the patient.

### 9.11.2 Previous therapy / medication with doxycycline

All previous treatments and medications with doxycycline during the last year before starting the trial will be documented in the CRF according to the memory of the patient.

### 9.11.3 Concomitant therapy / medication for other indications

All concomitant therapies/medications other than the trial IMP applied during the trial at the discretion of the trial clinician will be documented in the CRF including the following information:

- brand name,
- indication,
- dose per intake and units,
- route of administration,
- time/duration of treatment (start and stop date of treatment or ongoing instead of the stop date if treatment is still persisting at subject's termination visit)

### 9.11.4 Prohibited therapy / Concomitant medication

Diet: There is no dietary restriction and participants will be encouraged to eat within one hour prior to drug intake.

The following therapies / medications are not allowed to be applied during the treatment because of interaction with the trial drugs:

- antacids containing aluminium, magnesium or sucralfate
- other antibiotics than doxycycline
- sulfonylurea, coumarin (doxycycline increases the levels of the coumarin and sulfonylurea which might lead to an adverse event)

If it is important to start treatment with one of the above mentioned prohibited therapies, treatment with the trial drugs will be stopped to prevent the patient from the interactions.

Female patients will be informed in detail that oral contraceptives might not work due to interactions with doxycycline. They will only be included in the clinical trial if they agree to use other agreed methods of contraception.

During the whole study the use of diuretics is not recommended, as they will change the outcome of the measurement. Medication will lead to exclusion of patient data from the analysis.

During treatment and the 24 months follow-up period patients should not receive antifilarial drugs (except during MDA). Short courses of antibiotics are permitted for the treatment of ADLA attacks and infections such as UTI or URTI. Intake of all drugs other than the study drugs will be documented on the diary cards and every two months in the case report forms.

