### 7.8.3 Exclusion criteria

Patients are ineligible to participate in the trial, if they have any of the following:

1. No lymphedema or lymphedema stage 7
2. Age < 14 years or > 65 years
3. Body weight < 40 kg
4. Pregnant or breastfeeding women

5. Women of childbearing potential not using an agreed method of contraception (including abstinence; oral contraceptives are not allowed because of interaction with trial drugs)
6. Clinical or biologic evidence of hepatic or renal dysfunction or disease of the central nervous system (CNS)
7. Evidence of severe comorbidities except for features of filarial disease
8. Alcohol or drug abuse
9. History of adverse reactions to doxycycline or other tetracyclines
10. Any significant condition (including medical and psychological/ psychiatric disorder) which in the opinion of the study investigator might interfere with the conduct of the study
11. History of photosensitivity reactions after taking drugs.
12. Concomitant medication with antacids containing aluminium, magnesium or sucralfate and not able to discontinue
13. Concomitant medication with other antibiotics than doxycycline and not able to discontinue
14. Concomitant medication with diuretics or sulfonyleurea
15. Concomitant medication with coumarin

Laboratory values which will lead to exclusion

1. Haemoglobin < 8 g/dL
2. Neutrophil count < 2 000/mm^3
3. Platelet count < 100 000/mm^3
4. Creatinine > 2 times upper limit of normal
5. AST (GOT) > 2 times upper limit of normal
6. ALT (GPT) > 2 times upper limit of normal
7.  $\gamma$ -GT > 2 times upper limit of normal
8. Positive urine pregnancy test

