## 11.6 Populations to be analyzed

Different analysis populations will be prepared before de-blinding (Safety population (SAF), Intention-to-treat population (ITT), Per-Protocol population (PP)). The criteria for the exclusion of patients from any of the analysis populations will be defined in the Statistical Analysis Plan (SAP) and will be finalized prior to database lock. The exclusion of participants from the analysis populations will then be decided during the blind data review before unblinding and will be described in detail in the blind data review report.

Since this is a superiority trial the ITT population will be used for all endpoint analyses. The PP population will be used to confirm the results of the ITT analysis. The SAF population will be used for the analysis of adverse events.

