### 11.6.1 Intent-to treat (ITT) population

The ITT population will consist of all randomized patients in the groups to which they were randomly assigned and who took the study drugs at least once.

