### **11.10.3 Drop-out/Withdrawal during or after treatment**

Subjects dropping out of the trial after randomization during but also after treatment will be analysed using all available data (ITT analysis)..

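### Section 9.11.4 removes diuretic users from an unnamed analysis, which conflicts with the ITT rule in sections 11.6 and 11.6.1

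*Protocol*

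**What the plan says.** Protocol section 9.11.4 covers diuretics in two sentences. The first is "During the whole study the use of diuretics is not recommended, as they will change the outcome of the measurement". The second is "Medication will lead to exclusion of patient data from the analysis". The second follows directly on the first, so it refers to diuretic use. Its period is the whole study, and it names neither a population nor an endpoint.

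Diuretic use at entry already makes a person ineligible (section 7.8.3, the criterion beginning "Concomitant medication with diuretics or"). The sentence in 9.11.4 therefore acts on use that starts after enrolment.

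Section 11.6.1 defines the ITT population as "all randomized patients in the groups to which they were randomly assigned and who took the study drugs at least once". Section 11.6 gives that population its role: "Since this is a superiority trial the ITT population will be used for all endpoint analyses". On the per-protocol set, section 11.6 says: "The PP population will be used to confirm the results of the ITT analysis". Section 11.6 also leaves the criteria for exclusion from the analysis populations to the SAP, with individual decisions at a blind data review.

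**The concern.** The two rules cannot both be followed. Under 11.6 and 11.6.1, a randomised participant who took study drug and later used a diuretic belongs in every endpoint analysis. Under 9.11.4, that participant's data come out.

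The exclusion depends on something that happens after randomisation. The protocol itself links diuretics to the limb measurements, and a worsening leg is a plausible reason for starting one, although the protocol does not say so. If that link exists, removal is tied to the primary endpoint, which is stage progression at 24 months. The planned progression rates differ by arm (25% on placebo, 5% on DOX 200), so removal tied to progression would take out more placebo participants even with perfect blinding. The comparison would then no longer be between the groups as randomised.

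**Working it through.** **Text check.**

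- Section 9.11.4: diuretic use at any time in the study removes the participant's data; no population is named.
- Sections 11.6 and 11.6.1: ITT for all endpoint analyses; the only condition beyond randomisation is one intake of study drug.
- Section 11.10.4, on missed treatment days, shows how the protocol words a PP-only exclusion: those participants stay in the ITT analysis and leave the PP analysis, and the PP analysis is named.
- Section 10.11.1 likewise keeps women who become pregnant during treatment in the ITT set.
- Section 9.11.4 has no such limit.

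**Inputs for the size** (sections 11.3.1, 11.4.1 and 11.7.2): 84 evaluable per arm; progression of 25% on placebo, 5% on DOX 200 and 8% on DOX 100; two-sided 5% Fisher's exact test.

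**Reproducing the plan.** Exact Fisher power, enumerating both binomials with 84 per arm, is 95.5% for 5% against 25% and 81.4% for 8% against 25%. The protocol states 95% and more than 81%, so its figures hold.

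**Assumed scenario.** A fraction f of progressors is removed in every arm and no non-progressor is removed. For true progression p:

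- observed rate = p(1 − f) / (1 − pf)
- remaining n = 84(1 − pf), rounded

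Placebo at f = 20%: 0.25 × 0.8 / (1 − 0.05) = 0.200 / 0.950 = 21.1%, n = 79.8, rounded to 80. DOX 200: 0.040 / 0.990 = 4.0%, n = 83. DOX 100: 0.064 / 0.984 = 6.5%, n = 83.

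| f | Placebo rate (n) | DOX 200 rate (n) | DOX 100 rate (n) | Power DOX 200 | Power DOX 100 |
|---|---|---|---|---|---|
| 0 | 25.0% (84) | 5.0% (84) | 8.0% (84) | 95.5% | 81.4% |
| 10% | 23.1% (82) | 4.5% (84) | 7.3% (83) | 95.3% | 81.9% |
| 20% | 21.1% (80) | 4.0% (83) | 6.5% (83) | 92.6% | 76.4% |
| 30% | 18.9% (78) | 3.6% (83) | 5.7% (82) | 88.3% | 70.8% |

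At 10% the power is essentially unchanged. The small rise for DOX 100 arises because its own rate falls too and the test is discrete. The apparent difference between placebo and DOX 200 nevertheless shrinks at every step: from 20.0 points to 18.6, 17.0 and 15.4.

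**Extreme case.** If progressors are removed from placebo only, power at f = 10%, 20% and 30% is 93.6%, 87.3% and 76.4% for DOX 200, and 76.3%, 64.0% and 48.0% for DOX 100.

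**The case against.** The strongest reply is that the decision on exclusions lies elsewhere. Section 11.6 hands the criteria to the SAP and the individual decisions to a blind data review, and it makes ITT the set for all endpoint analyses. The words in 9.11.4 could then be read as meaning the PP analysis, and the SAP, which is not at hand, may say so. That reading is available, but it is not what the sentence says. The protocol names the PP analysis when it means it, and 9.11.4 already fixes an exclusion. An SAP that follows 9.11.4 departs from 11.6.1, and one that follows 11.6.1 departs from 9.11.4. A blind review makes exclusions blind to treatment but does not make them independent of outcome.

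Other parts of the reply stand:

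- No frequency of diuretic use and no reason for it is given. The link to worsening is an inference.
- A reader might infer that only placebo progressors would be deleted and take the extreme figures as the expected loss. The documents do not support that. Participants, care providers and outcome assessors are blinded (section 7.6.2), so if worsening prompts diuretic use, progressors on doxycycline would be affected too.
- A reader might also cite section 11.10.3, where data "will be analysed using all available data (ITT analysis"). That section concerns people who drop out. A diuretic user who attends at 24 months has not dropped out, so the conflict rests on 11.6 and 11.6.1.
- Keeping diuretic users is not free of cost, because the protocol says these drugs alter the measurement.

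**Conclusion.** The contradiction is in the text and does not depend on any assumed rate: an unqualified exclusion after randomisation in 9.11.4 stands against an ITT rule without a medication exception in 11.6 and 11.6.1. It decides who enters the primary analysis, so it should be settled before unblinding.

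The size is conditional. With 10% to 30% of progressors removed in every arm, and nobody else, placebo progression would be understated by 1.9 to 6.1 percentage points. Power would lie between 95.3% and 88.3% for DOX 200 and between 81.9% and 70.8% for DOX 100. If diuretic use is rare or unrelated to progression, the effect is small. It would be too strong to say that the trial will lose power or that the effect will be biased, since the documents give nothing from which to estimate either.

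**What to change.** Replace the last sentence of the diuretics paragraph in section 9.11.4 with:

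*Diuretic use is recorded and reported by arm. Participants who take diuretics remain in the ITT analysis with their observed stage; their exclusion is limited to the PP population and a sensitivity analysis, as decided at blind data review.*

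This agrees with sections 11.6, 11.6.1 and 11.10.4. It does not label diuretic use a protocol violation, because 9.11.4 only advises against it and does not place it on the list of drugs barred during treatment. No change to the clinical rule on diuretics is proposed.

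The cost is one amended sentence. No new data are needed, since 9.11.4 already requires all non-study drugs to be documented. The downside is that observed values in diuretic users may partly mask progression, and that masking could be related to outcome. The PP or sensitivity analysis without these participants addresses it. The planned power is fully kept only if diuretics leave the recorded stage unaffected, which the protocol does not establish.

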#### 8.1.7 Training for care and hygiene of affected legs and arms

All patients will be initiated to a programme of cleaning of the affected limb based on the principles outlined in the booklet “New Hope” for persons with lymphedema [3]. The regimens will be explained to all participants who will be trained to use established standardized methods of hygiene and be effectively applying it prior to the initiation of the drug treatment. Each patient will receive soap, towels and plastic bowls for washing the limbs and a diary for recording ADLA attacks. Community Health Volunteers will be engaged to assist persons who cannot read and write to record the ADLA attacks in the diary as done in our previous study [2]. Supplies will be replenished during the follow-up visits, if necessary.

A generic SOP with handouts that describes methods and the training schedule will be utilized so that similar methods are employed across all sites. In addition, patients will be retrained at 4, 6, 12, 18 and 24 months. This will be standardized by the investigators and will include the following:

1. Cleaning of the affected limb daily with soap and water
2. Keeping the affected limb dry
3. Clipping the nails
4. Appropriate antibiotics for ADLA episodes
5. Applying antifungal ointment to webs of the toes, nails and sides of the feet every night
6. Elevation of the affected extremity
7. Limb exercises as instructed
8. Encouraging and monitoring the use of appropriate footwear

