## 11.9 Protocol violations

Protocol violations are major deviations from the procedures outlined in this document like:

- non-compliance with investigational medicinal product (missing treatment days at the end of the treatment period (the treatment period should be prolonged for all days the patient was absent or did not get the trial drugs by decision of the trial clinician),
- intake of medications not allowed
- any non-adherence to the protocol that would have an impact to the subject’s rights, safety or welfare,
- absence from treatment for more than 3 consecutive treatment days (participants who are absent for more than 3 consecutive treatment days will be requested to finish the whole treatment).
- absence from treatment for more than 7 treatment days (treatment will be stopped if participants are absent for more than 7 treatment days, but the patients will be asked to come for the follow-ups).

After a subject has been enrolled, it is the investigator's responsibility to make a reasonable effort to prevent and correct any protocol violations if necessary and to continue the subject's participation in the trial, if possible. Protocol violations will be reported to the sponsor/sponsor delegated person during the course of the trial in the monitoring reports and reported to the Ethics Committees after completion of the trial. All protocol violations will be listed and the impact on the evaluation of the subjects concerned will be discussed prior to statistical analysis.

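### Section 9.11.4 tells staff both to stop study drug and to carry on when an ADLA attack or infection needs antibiotics during the 42 dosing days

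*Protocol*

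**What the plan says.** **The ban (9.11.4).** A list is introduced by "The following therapies / medications are not allowed to be applied during the treatment because of interaction with the trial drugs". One entry is "other antibiotics than doxycycline". If a listed therapy has to be started, "treatment with the trial drugs will be stopped to prevent the patient from the interactions".

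**The permission (9.11.4, last paragraph).** The paragraph begins "During treatment and the 24 months follow-up period patients should not receive antifilarial drugs (except during MDA"). The next sentence is "Short courses of antibiotics are permitted for the treatment of ADLA attacks and infections such as UTI or URTI". It names no period of its own.

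**The care package (8.1.7).** Item 4 is "Appropriate antibiotics for ADLA episodes", with no route of administration and no exception for the dosing weeks. Participants are to be "trained to use established standardized methods of hygiene and be effectively applying it prior to the initiation of the drug treatment".

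**Analysis consequences.** Section 11.9 counts "intake of medications not allowed" among the protocol violations, which it calls major deviations. It also lists missing treatment days at the end of the treatment period. Section 11.6.2 keeps anyone with a major deviation out of the per-protocol (PP) population, and 11.10.4 excludes from PP those who miss more than 3 consecutive treatment days. Section 11.6 uses ITT for all endpoint analyses and PP to confirm them. It leaves the detailed exclusion criteria to the SAP and the blind data review.

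**The concern.** A participant with an ADLA attack on, say, day 10 could be given an antibiotic and continue study drug under one sentence, or be taken off study drug under the other. The decision is made in the village by the trial clinician, so two clinicians could act in opposite ways and each point to the protocol.

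The trigger is not neutral. Frequency, duration and absence of acute attacks are secondary endpoints (7.7.2), and section 5 says that attacks drive the progression of lymphedema, which is the primary outcome. A stop rule triggered by ADLA shortens treatment in participants selected by their disease activity. If doxycycline already reduces attacks during dosing, it does so to a different extent in each arm.

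What is at stake is the exposure actually delivered, which every analysis reflects, and the make-up of the PP set that is meant to confirm the ITT result.

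**Working it through.** **Side by side, for an attack during dosing that is treated with a non-doxycycline antibiotic**

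| | Ban governs | Permission governs |
|---|---|---|
| Study drug | Stopped | Continued |
| Antibiotic | Not allowed alongside study drug | Allowed |
| 11.9 item on disallowed medication | Met if the antibiotic is taken while study drug continues; not clearly met if study drug is stopped as directed | Not met |
| PP status | Likely lost through incomplete treatment | Kept on this count |

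On incomplete treatment: there are 42 doses, and 11.10.4 excludes for more than 3 consecutive missed days. If a directed stop counts as missed days, anyone whose last dose is no. 38 or earlier misses at least 42 − 38 = 4 and leaves PP.

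**Does any text decide between the columns?** The ban is tied to the treatment period. The permission follows a sentence whose period is treatment plus 24 months. Section 8.1.7 sets no exception for the dosing weeks. Exclusion criterion 13 in 7.8.3 (unable to discontinue other antibiotics) fits the ban, but concerns entry and not attacks arising later. Nothing reconciles the two paragraphs.

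**How many could be affected?** The protocol gives no ADLA rate, so there is no figure of its own to reproduce. Inputs:
- dosing period: 42 days (synopsis and 8.3);
- group A arm size: 120 (7.3);
- attack rate r: assumed at 0.5, 1 and 2 per person-year, constant and equal across arms.

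The probability of at least one attack in 42 days is 1 − exp(−r × 42/365):

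| r per year | r × 42/365 | Probability | × 120 |
|---|---|---|---|
| 0.5 | 0.0575 | 5.6% | 6.7 |
| 1 | 0.1151 | 10.9% | 13.0 |
| 2 | 0.2301 | 20.6% | 24.7 |

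At each assumed rate the count is an upper bound for the ADLA route, because it supposes that every attack is treated with a non-doxycycline antibiotic. Courses for UTI or URTI fall under the same conflict and are not counted.

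The power figures in 11.4.1 are not in dispute. With 84 per arm and a two-sided Fisher test, exact power is 95.5% for 25% versus 5% and 81.4% for 25% versus 8%, in line with the stated 95% and > 81%.

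**The case against.** **A reading exists that reconciles the two.** The ban is limited to treatment and rests on drug interaction. The words about treatment and 24 months belong to the sentence on antifilarial drugs, and the antibiotic sentence has no period of its own. One can apply the ban to the dosing days and the permission to follow-up. That reading is fair, but the text does not state it and the paragraph's opening points the other way. Even on that reading, an outcome event would end treatment.

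**Section 8.1.7 is weaker support than it looks.** It gives no route, and sections 4 and 5 describe the package with topical antibiotics. This stands: 8.1.7 adds to the ambiguity but does not clearly prescribe the kind of course that the ban targets.

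**Per-protocol criteria belong to the SAP.** Section 11.6 says so, and the SAP could settle who is in PP. It cannot settle whether a participant's study drug was stopped.

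**Stronger readings that the protocol does not support:**
- A reader might infer that every participant given antibiotics for ADLA is a major-deviation case. A stop made as 9.11.4 directs follows the protocol and is not clearly the disallowed-medication item in 11.9.
- A reader might infer that the non-inferiority step of DOX 100 against DOX 200 is undermined through PP. Nothing assigns PP to that test; 11.6 uses ITT for all endpoints.
- A reader might infer that these participants are lost from ITT. Sections 11.6.1, 11.10.3 and 11.10.4 keep them in.

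**Conclusion.** The contradiction within 9.11.4 is real. For the dosing days the protocol supports opposite actions on study drug, and no other section resolves it. It should be corrected, but it does not invalidate the primary analysis, which is ITT on lymphedema stage at 24 months.

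The effects are on delivered exposure and, through incomplete treatment or 11.9, on the confirmatory PP set. Differential loss between arms is a possibility that depends on doxycycline reducing attacks within the dosing weeks; it has not been shown. The size is at most about 7, 13 or 25 of 120 per group A arm through ADLA, under the assumed rates and universal antibiotic treatment described above. The true number is unknown from the protocol.

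**What to change.** 1. Reconcile the two paragraphs of 9.11.4 with 8.1.7 and 11.9 into one rule for antibiotics during the dosing days, covering ADLA and other infections and saying whether topical and systemic use are treated alike. Which clinical rule applies is for the sponsor to decide.
2. Make the PP consequence in 11.9 and the SAP match that rule before unblinding, including whether a stop directed by the protocol counts as missed treatment days under 11.10.4.
3. Report, by arm, antibiotic courses during dosing with their indication, and the study-drug stops that resulted.

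The cost is wording in the protocol and SAP plus one table. Concomitant medication, with its indication and dates, is already recorded at each treatment day and follow-up visit, so no new data are needed. No change to the ITT definition is required.
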